## Abstract

**Introduction:**

NKR-2 are autologous T cells genetically modified to express a chimeric antigen receptor (CAR) comprising a fusion of the natural killer group 2D (NKG2D) receptor with the CD3ζ signalling domain, which associates with the adaptor molecule DNAX-activating protein of 10 kDa (DAP10) to provide co-stimulatory signal upon ligand binding. NKG2D binds eight different ligands expressed on the cell surface of many tumour cells and which are normally absent on non-neoplastic cells. In preclinical studies, NKR-2 demonstrated long-term antitumour activity towards a breadth of tumour indications, with maximum efficacy observed after multiple NKR-2 administrations. Importantly, NKR-2 targeted tumour cells and tumour neovasculature and the local tumour immunosuppressive microenvironment and this mechanism of action of NKR-2 was established in the absence of preconditioning.

**Methods and analysis:**

This open-label phase I study will assess the safety and clinical activity of NKR-2 treatment administered three times, with a 2-week interval between each administration in different tumour types. The study will contain two consecutive segments: a dose escalation phase followed by an expansion phase. The dose escalation study involves two arms, one in solid tumours (five specific indications) and one in haematological tumours (two specific indications) and will include three dose levels in each arm: 3×10^8^, 1×10^9^ and 3×10^9^ NKR-2 per injection. On the identification of the recommended dose in the first segment, based on dose-limiting toxicity occurrences, the study will expand to seven different cohorts examining the seven different tumour types separately. Clinical responses will be determined according to standard Response Evaluation Criteria In Solid Tumors (RECIST) criteria for solid tumours or international working group response criteria in haematological tumours.

**Ethics approval and dissemination:**

Ethical approval has been obtained at all sites. Written informed consent will be taken from all participants. The results of this study will be disseminated through presentation at international scientific conferences and reported in peer-reviewed scientific journals.

**Trial registration number:**

NCT03018405, EudraCT 2016-003312-12; Pre-result.

Strengths and limitations of this studyStandard dose escalation phase and an expansion phase to investigate for the first time the safety and initial clinical activity of NKR-2 (natural killer group 2D (NKG2D)-based chimeric antigen receptor (CAR) T cells retrovirally modified) in a multiple injection schedule.Phase I study exploiting the multiple ligand targeting capability of human NKG2D by assessing the safety and initial clinical activity of NKR-2 against a broad range of tumour indications, including haematological and solid tumour types.Based on the unique NKR-2 mode of action, NKR-2 will be administered without any prior preconditioning.

## Introduction

### CAR T cell therapy

The chimeric antigen receptor (CAR) is an artificial construct that endows T cells with predetermined specificity.^1^ Prior to adoptive transfer, they have to be expanded in vitro to reach therapeutically sufficient numbers. In this manner, large numbers of tumour antigen-specific T cells can be rapidly generated for use in adoptive cell therapy. The CAR itself has developed through several generations but has largely followed the configurations of extracellular antigen-binding domain (most commonly a single-chain variable fragment (scFv) derived from an antibody), a transmembrane domain and intracellular signalling domains. At present, second-generation formats tend to predominate featuring a co-stimulatory signalling domain (eg, CD28, 4-1BB) fused to a T cell-activating domain (eg, CD3ζ).^1 2^

The CD19-specific CAR provides the paradigm against which other CAR approaches are currently measured due to the impressive clinical responses seen in early phase clinical trials targeting B cell malignancies. Reports of initial objective clinical responses in 70–90% of patients with advanced chemoresistant B cell leukaemia have fuelled interest in the area with the number of CD19-targeted CAR T cell trials rapidly rising within the last few years.^3 4^ The CD19-CAR T cell therapy approach is based on a ‘*transplant procedure-like*’ approach, that is, a single CAR T cell infusion in preconditioned (lymphodepleted) patients and for which persistence, expansion and survival of the transferred T cells are crucial.^3 4^ All preconditioning regimens follow a similar concept where there is a transient depletion of circulating lymphoid cell populations to provide ‘space’ for the adoptively transferred T cells to occupy.^5 6^ Additional beneficial effects of preconditioning include the production of homeostatic cytokines and dampening of suppressive factors such as regulatory T cells, thereby providing a window of immunological opportunity to target the tumour.

However, single-target therapy may select for and spur escape variants by clonal selection or antigen loss. Several CD19-specific therapies indeed evidenced cases of relapse resulting from CD19 antigen loss in leukaemia cells post-CD19-specific CAR T cell therapy.^7–10^ Furthermore, these therapies are also associated with significant levels of toxicity,^11 12^ including cytokine release syndrome (CRS), neurotoxicity and on-target off-tumour toxicity against normal cells (eg, CD19-specific CAR T cells also target normal B cells expressing CD19, causing prolonged B cell aplasia and hypogammaglobulinaemia^13 14^). Moreover, anaphylaxis reaction to the foreign components of the CAR (eg, most CARs use scFv from murine origin, which might potentially induce transgene-specific humoural and cellular immune responses against the murine domain^15–17^) will impact drastically the safety of multiple injection schedule.^18^ The risk/benefit is clearly biased towards benefit since these patients have highly advanced cancer with little, if any, alternative effective therapeutic option. However, this toxicity does provide a level of patient selection that impacts recruitment onto current trials and the wider applicability for the general patient population.

By contrast, outside of the B cell malignancy setting, the CAR T cell approach has met with much reduced levels of clinical success.^2^ Notably, apart from CD19, there are only a few examples of normal cell lineages that can be safely eliminated along with malignant cells that share the targeted antigen, even within haematological malignancies. Targeting an antigen on tumour cells that is also present on normal cells, for example, on the myeloid lineage, could lead to on-target off-tumour toxicity and serious side effects related to therapy.^19^ Early studies targeting solid tumours reported little evidence of clinical effect while there was some evidence of on-target, off-tumour toxicity seen using CAR targeting carbonic anhydrase-IX^16 20^ in renal cell carcinoma or Her2/neu-specific CAR T cells in colorectal cancer (CRC).^21^ Investigators are therefore still seeking for the ideal target antigen that should be highly overexpressed on tumour cells compared with normal cells. While some recent studies have shown limited clinical effect but nowhere near to that seen with CD19 CAR T cell therapy,^3 22^ the challenges posed by solid tumours are numerous and have been extensively reviewed recently.^23–26^ In brief, these include the on-target off-tumours impact related to expression of the target on normal tissues, the need for trafficking into the tumour microenvironment (TME) and tumour stroma, tumour heterogeneity and the requirement to overcome the hostile immune suppressive TME, potentially leading to CAR T cell exhaustion, clearly requiring the further development of the basic CAR approach.^27^ Several options, including third-generation and fourth-generation CARs (eg, Armoured CAR, T cells redirected for universal cytokine-mediated killing (TRUCKs)), logic gated activation strategies or the combination of CAR T cells with T cell checkpoint inhibitors, are currently under development to solve these problems.

### NKR-2

NKR-2 are autologous T cells genetically modified to express a CAR comprising a fusion of the full-length natural killer group 2D (NKG2D) receptor with the CD3ζ signalling domain. NKG2D is a C-type, lectin-like, type II transmembrane glycoprotein-activating receptor expressed in humans on natural killer (NK), natural killer T, activated CD8^+^ T cells and, under certain conditions, some CD4^+^ and γδ+T cell subsets^28^ and functioning to target and kill cancer or infected cells. In humans, NKG2D is expressed as a homodimer that associates with the adaptor molecule DNAX-activating protein of 10 kDa (DAP10) to form a hexameric structure.^29^ The interaction with DAP10 is essential to stabilise the surface expression of NKG2D in T cells and to mediate signal transduction and cellular activation upon ligand recognition.^30^ Therefore, while the NKR-2 CAR format suggests a ‘first-generation’ configuration, the NKG2D structural component, via its interaction with endogenous DAP10, engages native T cell co-stimulatory signalling apparatus to providing a sufficient co-stimulatory signal which complements the primary CD3ζ vector-derived signal, indicating that the NKR-2 actually works rather like a ‘second-generation’ CAR (figure 1). Furthermore, the requirement for endogenous DAP10 expression for stable expression of NKG2D within cells defines an additional embedded safety measure to restrict NKR-2 vector expression and function specifically to cells expressing native DAP10 (eg, T cells).

**Figure 1 F1:**
[figure not shown]
The NKR-2 construct. NKR-2 design contains the full-length human natural killer group 2D (NKG2D) receptor linked to the signalling domain of CD3ζ that provides primary signalling (signal 1) to activate T cells upon ligand binding. The naturally expressed adaptor molecule DNAX-activating protein of 10 kDa (DAP10) provides secondary signalling (signal 2) which allows NKR-2 to work as a second-generation CAR.

In humans, eight NKG2D ligands have been identified, encoded by different loci on two different arms of the chromosome 6 and corresponding to two main families: the major histocompatibility complex (MHC) class I chain-related proteins (MIC) which include MICA and MICB proteins, and the structurally diverse unique long 16-binding proteins (UL16-binding proteins or ULBP) which include ULBPs 1 to 6.^31^ The expression of these ligands can be induced by stress such as viral infection, oxidative or thermal stress, genotoxic drugs, DNA-damaging agents, tissue damage, heat shock, inflamed tissues (eg, autoimmune diseases) and malignant transformation.^32^ Importantly, a broad range of primary tumours express NKG2D ligands.^33 34^ While the NKG2D ligand expression profile is often heterogeneous, the large majority of tumour samples express at least one ligand (and often multiple ligands), including haematological and solid tumour types, implying that the profile of ligand expression is suitable to be exploited as a cancer therapy.^34^ Finally, the surface expression of NKG2D ligands can be modulated by proteolytic cleavage with the release of the soluble ectodomain.^35 36^ These shed NKG2D ligands may downmodulate NKG2D expression on NK cells and T cells, contributing to tumour immune escape and elevated serum levels were accordingly often associated with poor prognosis.^35 36^

The breadth of ligands targeted by NKG2D provides T cells armed with the NKR-2 receptor the potential to challenge an extensive range of tumour indications.^33 34^

Preclinical studies have shown the murine equivalent of NKR-2 (chNKG2D T cells) can mediate potent antitumour activity against both haematological and solid tumours,^37^ including highly heterogeneous tumours with less than 10% ligand-positive tumour cells (see table 1 for a summary of these data).^38^

**Table 1 T1:** Preclinical studies with NKR-2

	Targeted model	Publications	Main findings
In vitro experiments			

**Figure 2 F2:**
[figure not shown]
NKR-2 different mechanisms of action. Apart from direct cytotoxicity against cancer cells, NKR-2 mode of action also involves reduction of blood vessel density indicative of an antiangiogenic activity, modulation of the immunosuppressive tumour microenvironment (TME) and induction of a long-term antitumour-specific memory immune response. MDSC, myeloid-derived suppressor cell.

Expressing the NKR-2 CAR into T cells therefore allows the NKR-2 cells to present the broad specificity characteristic of NK cells while exploiting the migration, expansion, long half-life and potential to generate immunological memory characteristic of T cells. In addition to direct recognition of tumour cells, targeting of ligands expressed on the stroma of the TME can also lead to disruption of the essential support mechanisms required for tumour cell survival and growth. Moreover, in contrast to other single or limited target CAR T cell therapies, the fact that NKR-2 targets several ligands from two main families putatively decreases the probability of target loss and associated relapse after treatment. Further, the lack of important in vivo cell expansion and long-term survival of NKR-2, and the induction of tumour-specific adaptive immunity in the absence of patient preconditioning, also bears a safety advantage preventing side effects generally associated with rapid CAR T cell expansion^50^ which often require development of strategies like embedded suicide systems or use of chemotherapy to eradicate the CAR T cells.^51 52^ Collectively, this suggests that exploiting the targeting of NKG2D ligands by NKR-2 to fight against diverse tumour indications with a single generic construct combining two features of innate and adaptive immunity provides potentially a new paradigm for CAR T cell therapy that the current protocol is designed to investigate.

## Methods and analysis

### Study objectives

The THerapeutic Immunotherapy with NKR-2 (THINK) trial is an open-label phase I study which primarily aims to assess the safety and clinical activity of the NKR-2 treatment administered three times every 2 weeks between each administration in different tumour types. The study is split into two segments each with specific study objectives. The first dose escalation segment focuses on determining the recommended dose (RecD) of NKR-2 cells for second segment of THINK. Segment 2 extends the safety study and also investigates initial clinical activity of NKR-2 across multiple tumour indications. In both segments, correlative measures of clinical activity will be examined.

### Study drug

NKR-2 refers to the viable autologous CD3^+^ cells obtained after transduction of autologous T cells with the NKG2D-based CAR, which contains a total viable population of at least 80% CD3^+^ cells, with at least 50% CD3^+^ being transduced. NKR-2 will be supplied cryopreserved in bags containing a T cell dose in accordance with the dose level which is to be administered.

### Rationale for the NKR-2 dose and regimen

NKR-2 has been used in the single infusion dose escalation clinical study CM-CS1 (NCT02203825) which evaluated the safety and clinical activity of NKR-2 administration without prior lymphodepleting conditioning in patients with two distinct haematological malignancies: acute myeloid leukaemia (AML)/higher risk myelodysplastic syndrome (MDS) refractory anaemia with excess blasts, that are not in remission and for which standard therapy options are not available, and relapsed or refractory progressive multiple myeloma (MM) after several lines of standard therapy. The trial has been successfully completed with no observed dose-limiting toxicities (DLTs) at the highest dose infused (3×10^7^ total cells) and initial signs of clinical benefit.^53^

In preclinical models, the pharmacologically effective dose (PED) of the murine NKR-2 ranged from 1×10^6^ cells to 7.5×10^6^ cells per dose (intravenous single injection). Although a significant antitumour activity was obtained with a single injection of murine NKR-2, 100% overall survival and complete recovery were obtained following repeated three sequential doses of 5×10^6^ cells/mouse without any adverse effect.^39 42 44 45^ Moreover, a treatment regimen with 2 weeks’ interval between injections was far more successful in terms of activity compared with a weekly interval demonstrating that successful treatment of established tumours did not require the administration of more NKR-2.^42^ The maximum tolerated dose (MTD) after a single intravenous injection was determined to be 1×10^7^ cells, and repeated administration of this dosage to healthy and tumour-bearing mice did not produce any major toxicities.^54^

Following these values of PED and MTD, the no-observed effect level was defined at 5×10^6^ cells/injection per mouse and were identical whatever the tumour-type model (haematological or solid tumour). Using the allometry scaling exponent of 0.75, as defined by Food and Drug Administration (FDA) guidelines (USFDA, 2005), human-equivalent PED and MTD were therefore estimated at 0.43–3.2×10^9^ and 4.3×10^9^ cells/injection, respectively. Together these observations of high tolerability in initial single dose phase I clinical trial coupled with preclinical efficacy experimentation strongly support the concept of a dose escalation segment of 3×10^8^ –3×10^9^ NKR-2 per infusion given three times each separated by a 14-day interval.

### Patient population

Refractory or relapsing patients with metastatic or locally advanced CRC, urothelial carcinoma, triple-negative breast cancer (TNBC), pancreatic cancer, recurrent epithelial ovarian and fallopian tube carcinoma, AML/MDS and MM, which failed from standard treatments, will be recruited into this protocol (the key inclusion and exclusion criteria are presented in box).BoxKey eligibility criteriaMain inclusion criteria:Men or women ≥18 years old at the time of signing the informed consent form (ICF).Patient with specific cancer indications (see below).Disease must be measurable according to the corresponding guidelines.Eastern Cooperative Oncology Group (ECOG) performance status of 0 or 1 or 2 based on peripheral neuropathy from prior therapies.Patient with adequate bone marrow reserve, hepatic and renal functions.Left ventricular ejection fraction of >40%.For patients with solid tumour type, the patient must agree to have a tumour biopsy at baseline.Main exclusion criteria:Patient with a tumour metastasis in the central nervous system.Patients who have received another cancer therapy within 2 weeks before the planned day for the apheresis.Patients who receive or are planned to receive any other investigational product within the 3 weeks before the planned day for the first NKR-2 administration.Patients who are planned to receive concurrent growth factor, systemic steroid or other immunosuppressive therapy or cytotoxic agent.Patients who underwent major surgery within 4 weeks before the planned day for the first NKR-2 administration.Patients who have active infections necessitating the use of antibiotics/antivirals treatment.Patients with history of autoimmune disease.Disease-specific inclusion criteria**Patients must have either:**A documented metastatic or locally advanced colorectal adenocarcinoma and having received, being intolerant or having refused at least two prior standard cancer therapy regimens as part of their primary treatment regimen or part of their treatment for management of recurrent/persistent disease.A documented recurrent epithelial ovarian cancer or fallopian tube carcinoma and having received or refused at least two prior standard cancer chemotherapy regimens as part of their primary treatment regimen or part of their treatment for management of recurrent/persistent disease.An inoperable locally advanced or metastatic urothelial carcinoma that has progressed after previous platinum-based chemotherapy.A metastatic or locally advanced triple-negative breast cancer and having received at least one prior cancer therapy regimen as part of their treatment for management of recurrent/persistent disease.A metastatic or locally advanced pancreatic ductal adenocarcinoma and having received, being intolerant or having refused at maximum two prior lines of standard cancer chemotherapy regimens.Relapsed or refractory acute myeloid leukaemia (ie, ≥5% blasts in bone marrow or in peripheral blood) after one prior therapy or patients with myelodysplastic syndrome (ie, ≥5% blasts in bone marrow or ≥2% blasts in peripheral blood) or MDS with TP53 mutation who failed from prior treatments.Relapsing or refractory/relapsing multiple myeloma with a minimum of one prior line of systemic therapy.

The study will enrol patients in different countries in Europe and in USA with a dose escalation segment open to a restricted academic network in Belgium and USA. List of study sites can be obtained on clinicaltrials.gov (NCT03018405).

The tumour types targeted in this protocol were selected primarily based on their high expression of the NKG2D ligands (with a prevalence of 78–100% tumour samples expressing at least one ligand).^33 34^ Furthermore, NKG2D ligand expression is a dynamic and context-dependent process, quickly varying over time in response to cytokines in the TME and evolving along with tumour progression, local inflammatory responses and treatments,^33 34^ hence difficult to assess. Finally, even if NKG2D ligand expression is heterogeneous with respect to the exact ligands found, based on preclinical data, potential therapeutic benefit might be achieved in patients with highly heterogeneous tumours^38^ or even tumours considered as ‘negative’ for NKG2D ligands because of a NKG2D ligand-positive TME and/or neovasculature and/or activation of host immune system.^42–48^ Thus, no eligibility criteria were based on the individual expression profile of NKG2D ligands and no diagnostic test for ligand expression was used for recruitment into this study. Correlative studies, however, will be carried out during the trial and will attempt to investigate the expression profile of patient tumours with clinical response.

### THINK study design

THINK phase I study will contain two consecutive segments: a dose escalation and an expansion segment (figure 3).

**Figure 3 F3:**
[figure not shown]
Overview of the study design. AML, acute myeloid leukaemia; CRC, colorectal cancer; MDS, higher risk myelodysplastic syndrome; MM, multiple myeloma; ORR, objective response rate; RecD, recommended dose; TNBC, triple-negative breast cancer.

The *dose escalation* design will include three dose levels of NKR-2. The assumption is made that the safety profile of the treatment could be different in haematological versus solid tumour types. Therefore, it will be assessed separately in two different arms, one in solid tumours (CRC, urothelial carcinoma, TNBC, pancreatic cancer or epithelial ovarian and fallopian tube carcinoma) and one in haematological tumours (AML/MDS or MM). Each arm will use a 3+3 design to determine the RecD of the NKR-2 treatment for the corresponding cohorts in the expansion segment, as based on the occurrence of DLTs (ie, three patients will be evaluated per dose level for each arm of the segment and three additional patients will be added if one out of three patients in this cohort experiences a DLT to further assess the safety of the treatment). The sample size of the dose escalation part will be between 2 and 18 patients per arm. Six patients will be treated at the MTD (or highest dose level if no DLT was observed).

The RecD will be the MTD unless in case no MTD is determined in the dose escalation segment of the study. In the latter, the RecD will be highest dose evaluated in the dose escalation segment.

The RecD will be further evaluated in the *expansion segment* of the study to assess separately the safety profile and initial clinical activity of the NKR-2 treatment in seven cohorts of patients with the distinct tumour types (up to 14 patients per tumour type). The expansion segment in haematological and solid tumours will be initiated as soon as their respective dose escalation arm defines the RecD. During this segment, the RecD can still be adapted according to predefined safety rules in any specific tumour type. The statistical analysis is planned in three steps. A futility analysis will be conducted separately in the first 14 patients with a solid tumour and the first 6 patients with a haematological tumour type. These number of patients have been defined to have a 0.05 probability of finding 0 objective response at this step if the true probability of response were 0.2 (solid) or 0.4 (haematological). Subsequently, futility (no response in the first seven patients) and efficacy (three or more responses in 14 patients) will be tested by cohort, based on the Simon’s two-stage optimal design. The assumptions are: type I error rate=0.15, power=0.80 and response probability of poor drug=0.10/beneficial drug=0.30. In total, up to 86 patients are expected to be enrolled in the expansion segment (in addition, the six patients from each arm of the dose escalation segment who were treated at the RecD will be included in these expansion analyses).

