In the dose escalation segment, safety data will be monitored closely on an ongoing basis. The main analysis (leading to the selection of the RecD) will be conducted separately in each arm once all patients in the last dose level have received the three NKR-2 administrations and have completed the safety period (D43). All data related to the primary endpoints of the study will be analysed. The final analysis will be performed once all patients have attended the concluding visit of the follow-up phase (M24) or have been withdrawn from the study.

The expansion segment of the study will proceed in three steps, with a statistical analysis at the end of each step (figure 3). These steps aim to stop the study for futility in specific cohorts or specific tumour types in case of no (sufficient) responders in the corresponding cohorts at the time of analysis.

An interim analysis for futility will be performed on the first 14 patients over all 5 cohorts of patients with solid tumour types and on the first 6 patients over the 2 cohorts of patients with haematological tumour types who have either completed the administration phase (D57) or have withdrawn from the study.

The second step consists in cohort futility analyses after the first seven cancer patients in each tumour type have either completed the administration phase (D57) or have withdrawn from the study. At this step, an evaluation of the safety of the NKR-2 treatment in each cohort will also be performed on the first six patients who completed the 6-week treatment period (D43) or had a DLT. This will allow to adapt the RecD in any specific cohort (tumour type) according to both safety rules and futility analysis. Indeed, if, and as soon as, two or more DLTs have been reported within a specific cohort, and the criterion for futility was not reached, the next patients enrolled in this cohort will be treated at the next lower dose level. In contrast, if no DLT has been reported within a specific cohort, and the criterion for futility was not reached at Step 2, the next patients enrolled will be treated with the next higher dose level.

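### The stated 0.80 cohort power leaves out the pooled Step 1 futility look; with it, power in each haematological cohort is about 0.74 at the plan's own beneficial rate of 0.30

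*Protocol article*

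**What the plan says.** The THINK study design section of the protocol article plans the expansion analysis in three steps.

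- **Step 1** is a futility look in "the first 14 patients with a solid tumour and the first 6 patients with a haematological tumour type". The sizes are chosen for a "0.05 probability of finding 0 objective response at this step if the true probability of response were 0.2 (solid) or 0.4 (haematological" arm. The stopping rule implied is no response. The interim-analysis text, printed under the Demographic characteristics heading, confirms that the haematological look is taken "on the first 6 patients over the 2 cohorts of patients with haematological tumour types".
- **Steps 2 and 3** work by tumour type: "futility (no response in the first seven patients) and efficacy (three or more responses in 14 patients) will be tested by cohort". One set of assumptions serves all seven cohorts: "type I error rate=0.15, power=0.80 and response probability of poor drug=0.10/beneficial drug=0.30".

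The purpose of the three steps is given as follows: "These steps aim to stop the study for futility in specific cohorts or specific tumour types in case of no (sufficient) responders". The text does not call Step 1 advisory, and it does not say that 0.80 is conditional on passing Step 1.

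Two further statements bear on who the first six haematological patients are. The design section says that "the six patients from each arm of the dose escalation segment who were treated at the RecD will be included in these expansion analyses". The Enrolment rules section asks for at least two cancer types at each escalation dose level, and the haematological arm has only two.

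**The concern.** The two haematological rules aim at different response rates. The pooled look has its 0.05 false-stop probability at 0.40, while the cohort test that follows is meant to detect 0.30. A haematological cohort at 0.30 can therefore be closed by a look that was never sized for that rate, and the quoted power does not count this loss. In the solid arm the order is reversed, because the look is anchored at 0.20, below 0.30.

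At stake is the chance of dropping AML/MDS or MM when it has exactly the activity the plan calls beneficial. Six consecutive non-responders, in any mix of the two diseases, would end both cohorts.

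**Working it through.** **Inputs from the protocol article.** Step 1 haematological: n = 6, stop at 0 responses. Step 1 solid: n = 14, stop at 0. Cohort rule: stop at 0/7, success at 3 or more of 14. Poor rate 0.10, beneficial rate 0.30.

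**Input not given.** The number k of the six Step 1 patients who come from the cohort of interest; k = 0 to 6 is shown.

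**1. The plan's own figures reproduce.**
- Step 1 false stop: 0.8^14 = 0.044 (solid) and 0.6^6 = 0.047 (haematological), both about 0.05.
- Simon rule: P(success) = Σ over x = 1 to 7 of P(X = x) × P(Y ≥ 3 − x), with X and Y independent Bin(7, p).
- At p = 0.30: 0.2471 × 0.6706 + 0.3177 × 0.9176 + 0.3529 = 0.810.
- At p = 0.10: 0.3720 × 0.1497 + 0.1240 × 0.5217 + 0.0257 = 0.146.

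A grid search confirms 0/7, 2/14 as the Simon optimal design for 0.10/0.30/0.15/0.80.

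**2. Step 1 at the beneficial rate.** With both haematological cohorts at 0.30, P(0/6) = 0.7^6 = 0.118. If one is at 0.30 and the other at 0.10, a 3/3 split gives 0.7^3 × 0.9^3 = 0.250.

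**3. Power through all steps.** Let q be the other cohort's rate. The look removes those outcomes in which the cohort would have succeeded but none of the six had responded:

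Power = 0.8101 − 0.7^k × A(k) × (1 − q)^(6−k)

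A(k) is the probability of cohort success given no response in its first k patients. It is the sum in item 1 with X ~ Bin(7 − k, 0.30). For k = 3:

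A(3) = 0.4116 × 0.6706 + 0.2646 × 0.9176 + 0.0837 = 0.6025

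- q = 0.30: 0.8101 − 0.343 × 0.6025 × 0.343 = 0.739
- q = 0.10: 0.8101 − 0.343 × 0.6025 × 0.729 = 0.659

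A simulation with 2,000,000 replicates gave 0.739 and 0.659 for these two cases.

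| k | both at 0.30 | other at 0.10 |
|---|---|---|
| 0 | 0.715 | 0.380 |
| 1 | 0.721 | 0.498 |
| 2 | 0.729 | 0.589 |
| 3 | 0.739 | 0.659 |
| 4 | 0.752 | 0.714 |
| 5 | 0.767 | 0.755 |
| 6 | 0.786 | 0.786 |

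**4. Which splits are plausible.** Seven cohorts of 14 make 98, and 98 − 12 = 86, the stated expansion enrolment. So the six patients per arm treated at the recommended dose do count towards the cohorts. If they are also the first six for Step 1, and both cancers are represented as the Enrolment rules ask, then k runs from 1 to 5. The range is 0.72 to 0.77 with both cohorts at 0.30, and 0.50 to 0.76 with the other at 0.10.

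**5. Solid arm for comparison.** With all solid cohorts at 0.30, P(0/14) = 0.7^14 = 0.007 and cohort power is 0.805 to 0.810.

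**The case against.** Every stated figure is right on its own terms, and 0.80 is listed as an assumption of the Simon design, which governs Steps 2 and 3. A reader might infer that the protocol claims 0.80 across all three steps and has miscalculated it. The text does not support that, since it never gives a three-step power. What stands is narrower: the only power quoted leaves out a stopping step that comes first, and nothing tells the reader so.

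Different rates at the two levels need not be an error either. Step 1 asks whether a tumour class shows any activity, and 0.40 may be a deliberate expectation for haematological disease. If both cohorts are truly at 0.40, cohort power through all steps is 0.900 to 0.928. But then the common beneficial rate of 0.30 does not describe these cohorts, and the article gives no reason for having both figures.

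The loss also depends on Step 1 being binding. The Ethics and dissemination section has the futility analyses reviewed by the sponsor's team with a steering committee whose role is advisory. Binding is the more natural reading of steps meant to stop cohorts, but it is not stated outright.

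A reader might also take 0.38 as the live worst case. It requires all six Step 1 patients to come from the inactive cohort, which is implausible given the enrolment rule and the counting of escalation patients. The 0.786 at the other extreme is implausible for the same reason.

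**Conclusion.** The point holds at moderate severity. If Step 1 is binding and both haematological cohorts have a true rate of 0.30, power in each is about 0.74 with a 3/3 split and 0.72 to 0.77 with both cancers among the first six. It is below 0.80 at every conceivable split (0.715 to 0.786). At 3/3 the chance of missing a beneficial cohort rises from 0.19 to 0.26. If only one cohort is active and the other is at 0.10, power is about 0.66 at 3/3; that is a scenario built from the plan's poor rate, not a forecast.

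Type I error is not inflated: with Step 1 included and both cohorts at 0.10 it is 0.068 to 0.138. The finding concerns an unquoted loss of power in two of seven cohorts of a phase I expansion. It does not invalidate the design.

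**What to change.** State whether Step 1 is binding, and quote haematological cohort power with Step 1 included: about 0.74 (0.72 to 0.77) with both cohorts at 0.30, and about 0.66 at a 3/3 split if only one is active. If 0.40 was chosen deliberately, give the reason and reconcile it with the cohort rate of 0.30. This costs wording only.

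As an option, size the haematological look at the plan's own 0.30. Nine patients are needed (0.7^8 = 0.058; 0.7^9 = 0.040). With a 4/5 split and both cohorts at 0.30, cohort power is 0.790 and 0.795, close to 0.80 but not fully there. The first look comes up to three patients later, within the existing maximum of 2 × 14 = 28. The look also stops two inactive cohorts less often: at 0.10 in both, 0.9^9 = 0.387 instead of 0.9^6 = 0.531.

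Removing the haematological look would restore 0.810, since the 0/7 rule still covers futility by cohort. It would give up the early pooled stop, so it is a trade-off and not a plain correction.
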